### Evaluation

To assess the impact of the EDMHCP implementation and explore the factors leading to our eventual findings, we have planned a mixed methods evaluation approach employing both quantitative and qualitative evaluations, as summarized in Table 3 and described further below. Additionally, a concurrent process evaluation will be conducted to assess the degree of variability and fidelity in implementation of the intervention within each dyad. This evaluation will include a process log, post-implementation site visits, and qualitative interviews.

**Table 3 Tab3:** Evaluation components

Quantitative evaluation	Qualitative evaluation
Patient chart audits	Patient surveys
Administrative data	Process evaluation Process log Post-implementation Site visits Key informant interview Focus groups
Patient surveys	

### Outcome measures

Table 4 provides a summary of study outcomes with the corresponding evaluation measures. The primary *process* outcome is the proportion of patients with documented MH-specific recommendations, as defined by the project team and based on the EDMHCP, in the medical chart. The primary MH *service* outcome is the proportion of patients that receive the EDMHCP recommended follow-up: either within 24 h or 7 days post-ED visit, based on pathway defined risk level. Recognizing logistic and scheduling factors, a successful outcome will permit a 12-h or 3-day window for follow-up. Adherence, within-window adherence, and non-adherence will be analyzed separately. Secondary outcomes include (1) EDMHCP uptake in the ED, measured as the proportion of completed clinical pathway forms filed in the health record; (2) post-ED uptake of recommended community MH services, as measured by the Services for Children and Adolescent-Parent Interview (SCA-PI) tool [21]; (3) alignment of recommended services to the HEADS-ED assessment; (4) ED length of stay, hospital admissions, ED revisits (10 days and 3 months) obtained from health records and National Ambulatory Care Reporting System (NACRS) data; and (5) patient/caregiver satisfaction with the ED visit as measured by the Services for Children and Adolescent-Parent Interview (SCA-PI) [22] and the Client Satisfaction Questionnaire (CSQ-8) [23].

**Table 4 Tab4:** Study outcomes: process and service

Outcome measure		Description	Details	Data source
Process outcomes	1°	Documented MH recommendations	Proportion of patients with documented MH-specific recommendations in the medical chart	Health record audits
	2°	EDMHCP uptake in the ED	Measured as the proportion of completed CPs filed in health records	Health record audits
Service outcomes	1°	Patients receiving post-ED follow-up	Proportion of patients that receive post-ED follow-up as per EDMHCP recommendations	Health record audits
				NACRS
				Telephone follow-up
	2°	Patient perspectives of post-ED MH service uptake	Post-ED uptake of recommended community MH services	Services for Children and Adolescent-Parent Interview (SCA-PI)
		Alignment of risk assessment with MH services recommendations	Alignment of recommended services to the HEADS-ED assessment	Health record audits
				NACRS
		Hospital metrics	ED LOS, hospital admissions, ED revisits (10 days, 3 months)	Health record audits
				NACRS
		Patient satisfaction	Patient/caregiver satisfaction with the ED visit	Client Satisfaction Questionnaire (CSQ-8)

*MH* mental health, *EDMHCP* Emergency Department Mental Health Clinical Pathway, *NACRS* National Ambulatory Care Reporting System, *ED LOS* emergency department length of stay

#### Health record audits

To evaluate whether the intervention results in EDMHCP use among ED clinicians and documentation of MH-specific discharge recommendations, we will audit health records of relevant patients seen during alternate weeks in each 9-month pre- and post-implementation period. ICD10 codes (F codes, mental, and behavior disorders; X codes, intentional self-poisoning and self-harm; Y codes, poisoning and self-harm of undetermined intent) listed as primary or secondary diagnoses will identify relevant patient charts during the study period. Abstracted data will include demographic and sufficient clinical data to determine risk assessment, disposition plans, and adherence with EDMHCP recommendations. Two auditors, blinded to the study aims and protocol, will be trained to abstract and directly enter health records data into REDCap, an online database [24]. A data dictionary will be created to guide auditors and ensure standardized data collection procedures. Auditors will each abstract the same 50 charts to assess inter-rater agreement. This will be measured for key variables with a kappa coefficient and further training will be done until a prevalence and bias-adjusted kappa >0.6 is achieved.

Based on historical administrative data, the number of pediatric MH visits at the pediatric specialized center is expected to be approximately 2250 during each 9-month period. This sample size will permit estimation of a proportion at this site to within ± 2.1 %, conservatively assuming a true proportion of 50 %. At the other extreme, the lowest number of pediatric MH visits during each 9-month period among the other three sites is expected to be approximately 61 at the rural hospital, which will permit estimation of a proportion to within ±12.5 %. Pooling across sites, the total sample size in each 9-month period is anticipated to be approximately 2503, which will permit estimation of a proportion to within ± 2.0 %.

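### The chart-audit precision figures count every mental health visit in nine months, although charts are audited only in alternate weeks; the half-widths for the audited sample are about 41% wider than stated

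*Protocol article*

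**What the plan says.** Both statements stand in the protocol article, section Health record audits.

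The first paragraph sets the sampling: "we will audit health records of relevant patients seen during alternate weeks in each 9-month pre- and post-implementation period".

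The second paragraph gives the precision. It starts from historical administrative data: "the number of pediatric MH visits at the pediatric specialized center is expected to be approximately 2250 during each 9-month period". It then treats that count as the sample: "This sample size will permit estimation of a proportion at this site to within ± 2.1" percent, "conservatively assuming a true proportion of 50" percent. The rural hospital follows in the same way, with a count "expected to be approximately 61 at the rural hospital", "which will permit estimation of a proportion to within ±12.5" percent. For all sites together, "the total sample size in each 9-month period is anticipated to be approximately 2503", with a stated half-width of 2.0 percent.

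Table 4 lists health record audits as the only data source for the primary process outcome (documented mental health recommendations). For the primary service outcome (follow-up as the pathway recommends) it lists health record audits, NACRS and telephone follow-up.

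**The concern.** Auditing alternate weeks gives roughly half of the period's visits, yet the precision paragraph uses all of them. Both statements cannot describe the same audited sample.

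This is the only sample-size or precision statement in the article. A reader would take it as what the audit delivers for documented recommendations, both overall and at each site. The Quantitative analysis section also plans pre and post proportions for each hospital, so the site-level figures bear on results that will be reported. The gap matters most at the rural hospital, where the stated interval is already wide.

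**Working it through.** **Inputs**
- Expected visits per nine-month period: 2250 (pediatric center), 61 (rural hospital), 2503 (pooled), from Health record audits.
- True proportion: 50%, from the same section.
- Confidence level: not given there. I take 95%, two-sided, from the Quantitative analysis section, so z = 1.96.
- Sampling fraction: alternate weeks, taken as 1/2. This assumes that visits are spread evenly over weeks.

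**Formula**

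Half-width in points = 100 × 1.96 × √(0.25/n).

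**Step 1: reproduce the stated figures with all visits**

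| Level | n | Computed | Stated |
|---|---|---|---|
| Pediatric center | 2250 | 2.07 | 2.1 |
| Rural hospital | 61 | 12.55 | 12.5 |
| Pooled | 2503 | 1.96 | 2.0 |

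All three agree to rounding. A 90% level does not reproduce them (1.73, 10.53, 1.64), nor does combining the pre and post periods (1.46, 8.87, 1.39). A Wilson interval for n = 61 gives 12.17, which also does not match. The stated figures therefore rest on the full visit counts at the 95% level.

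**Step 2: the same formula with half the visits**

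| Level | Audited n | Half-width | Stated |
|---|---|---|---|
| Pediatric center | 2250/2 = 1125 | 2.92 | 2.1 |
| Rural hospital | 61/2 = 30.5 | 17.7 (17.9 at n = 30, 17.6 at n = 31) | 12.5 |
| Pooled | 2503/2 = 1251.5 | 2.77 | 2.0 |

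Halving n multiplies each half-width by √2 = 1.41, so each is about 41% wider.

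**Step 3: charts needed for the stated figures**

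Solving n = (1.96 × 0.5 / half-width)² gives about 2178 charts for ±2.1 points, 61 for ±12.5 and 2401 for ±2.0. Each is roughly twice what alternate-week auditing would yield.

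**The case against.** **The counts may already be halved.** If 2250, 61 and 2503 covered only the audited weeks, the half-widths would stand. The wording does not support this: it speaks of visits over each nine-month period, takes them from historical administrative data, and mentions no reduction. The authors could still confirm it, and the text would then need a sentence saying so.

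**A finite-population correction gives the same numbers.** At a sampling fraction of one half, the correction √(1 − 1/2) exactly cancels the √2. The algebra is right, but the section states no such correction and calls the full count the sample size. The study also aims at the effect of the pathway, not at a census of one period's visits.

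**The practical effect is modest.** At the pediatric center, which has 2250/2503 = 90% of visits, and for the pooled estimate, the change is less than one point. The figures set no recruitment target and no stopping rule. This stands, and it limits the severity.

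**Stronger readings that the document does not support**
- *That both primary outcomes lose half their sample.* The service outcome also uses NACRS and telephone follow-up, and neither is described as limited to alternate weeks. Charts may be needed to assign risk level, but a halved sample for this outcome is an inference.
- *That the rural site could show no plausible change.* With 30 charts per period, Fisher's exact test gives p = 0.029 for 20% against 50% (6/30 against 15/30) and p = 0.015 for 10% against 40% (3/30 against 12/30). The article gives no baseline or target, and it says the sites do not currently use clinical pathways, so shifts of that size cannot be ruled out.
- *That multiplying by √2 once more gives the precision of the pre-to-post effect.* The planned analysis is segmented regression with an ARIMA autocorrelation structure, adjusted for site, together with an unweighted mean of change. A simple two-period difference matches neither. The section claims precision only for a single proportion, and a condensed article need not give more.
- *That visits are wrongly counted as patients.* The article gives no repeat-visit rate, so no size can be put on this.

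**Conclusion.** The stated precision is wrong as written for the sample the section describes. With alternate-week auditing, the half-widths for one proportion in one period are about ±2.9 points at the pediatric center, ±17.7 at the rural hospital and ±2.8 pooled, in place of ±2.1, ±12.5 and ±2.0. The effect is certain for the primary process outcome and not established for the primary service outcome.

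The result assumes an even spread of visits over weeks, a true proportion of 50%, a 95% level, independent observations, and visit counts that are not already restricted to audited weeks. Exclusions, repeat visits by the same child, or clustering would in general widen the intervals further, but the article gives no figures for these.

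This is a should-fix point. The error is plain and cheap to correct, and it is material for the rural site, but it does not undermine the design.

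**What to change.** In Health record audits, make the sampling sentence and the precision paragraph describe the same charts. One of three changes does this:

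1. If alternate weeks are audited and the counts are all visits, restate the expected audited charts per period as about 1125 (pediatric center), 30 (rural hospital) and 1250 (pooled), with half-widths of about ±2.9, ±17.7 and ±2.8 points. State the 95% level and the assumption of an even spread over weeks.
2. If the counts already cover only the audited weeks, say so and keep the half-widths.
3. If all weeks are to be audited, correct the sampling sentence and keep the half-widths.

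The first two changes cost wording only, and under the first the stated figures become less favorable. The third is also only wording if full auditing is already the intention; otherwise it roughly doubles the charts to abstract.

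Auditing every week at the small sites only is a possible design choice but is not needed to correct the error. It would give unequal sampling fractions, so pooled proportions would need weighting and the time-series intervals would need aligning.

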### Analysis

#### Quantitative analysis

Descriptive statistics (means and standard deviations for continuous variables or medians with interquartile ranges) will summarize EDs, CMHAs, and patient characteristics. Frequencies and proportions for categorical variables will be reported. We will use a multiple baseline study design and conduct interrupted time-series analysis using segmented regression models, adjusting for site, with ARIMA autocorrelation structure [25–27] to evaluate whether the EDMHCP has resulted in improved health care utilization, medical management, and health sector coordination. Two-sided *p* values less than 0.05 will be considered statistically significant. Model estimates will be tabulated, together with 95 % confidence intervals. We will also calculate hospital level summary measures including proportions in the pre- and post-intervention periods at each site and referred to each CMHA. An unweighted mean of the change from pre- to post-intervention will be calculated for each hospital ED. The main effect measure will be calculated as the difference between the mean changes in intervention.

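### One alternate-week audit rule for all four EDs halves the chart count at three low-volume EDs, where a full audit would cost only about 10% more charts

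*Protocol article*

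**What the plan says.** The Health record audits section sets one sampling rule: "we will audit health records of relevant patients seen during alternate weeks in each 9-month pre- and post-implementation period". It does not vary by site, and the article gives no reason for subsampling the smaller sites.

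The same section gives expected volumes. At the largest site, "the number of pediatric MH visits at the pediatric specialized center is expected to be approximately 2250 during each 9-month period". The smallest is put at "approximately 61 at the rural hospital". Across all sites, "the total sample size in each 9-month period is anticipated to be approximately 2503". The margins quoted with these counts are ±2.1%, ±12.5% and ±2.0%, "conservatively assuming a true proportion of 50"%.

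Quantitative analysis names a site-adjusted segmented regression first. It then plans pre and post proportions at each site, and adds: "An unweighted mean of the change from pre- to post-intervention will be calculated for each hospital ED". A main effect measure is to be built from the mean changes.

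In Table 4 the audit is the only data source for the primary process outcome. It is one of three for the primary service outcome, beside NACRS and telephone follow-up.

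**The concern.** Sampling alternate weeks saves real work at a site with 2250 visits. At a site with 61 visits it saves about 30 charts and discards half of a scarce sample. The common rule places about 90% of the audited charts at one ED. Yet the study chose four contrasting EDs and plans to report each one's change, and an unweighted summary counts each ED the same whatever its chart count.

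The precision of the site-level results, and of any equally weighted summary, is therefore set almost entirely by the three EDs where charts are fewest and cheapest to audit in full. "Low-volume" here means pediatric MH visits; two of the three have total ED censuses of 60,000 and 75,000.

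**Working it through.** **Inputs.** From Health record audits: 2250 visits at the centre, 61 at the rural ED, 2503 in total, p = 0.5, and an audit fraction of 1/2. From Quantitative analysis: two-sided 5% level and 95% intervals. The two remaining EDs share 2503 − 2250 − 61 = 192 visits. Their split is not given. Since 61 is the lowest count, it lies between 61/131 and 96/96; 96/96 is assumed below unless stated.

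**Step 1: the plan's own figures.** Half-width = 1.96 × √(0.25/n).
- n = 2250: 2.07; n = 61: 12.55; n = 2503: 1.96. These match ±2.1, ±12.5 and ±2.0 to rounding.
- With alternate weeks, n = 1125: 2.92; n = 30.5: 17.7; n = 1251.5: 2.77.

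So the stated margins hold only if every counted visit is audited, or if the counts are already halved. The article does not say which. The steps below take them as full counts; step 6 takes the other reading.

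**Step 2: allocation.** Alternate weeks everywhere gives 1125, 30.5, 48 and 48 charts, 1251.5 in all; 1125/1251.5 = 89.9% are at the centre. Full audit at the three low-volume EDs with alternate weeks at the centre gives 1125, 61, 96 and 96, in all 1378. The difference is 126.5 charts per period, or 126.5/1251.5 = 10.1%.

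**Step 3: unweighted four-ED mean change.** Half-width = (1.96/4) × √(0.5 × Σ1/n), with p = 0.5 before and after.
- Now: Σ1/n = 0.00089 + 0.03279 + 0.02083 + 0.02083 = 0.07534; half-width 9.51 points. The three low-volume EDs supply 98.8% of the sum.
- Three EDs in full: Σ1/n = 0.00089 + 0.01639 + 0.01042 + 0.01042 = 0.03812; half-width 6.76 points.
- Narrowing: 1 − 6.76/9.51 = 28.9%. With a 61/131 split it is 9.91 to 7.04 points, again 28.9%.

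**Step 4: pooled proportion, weighted by inverse sampling fraction.** With W the site's share of visits (0.899, 0.024, 0.038, 0.038), half-width = 1.96 × √(0.25 × ΣW²/n). Now 2.77; with the three EDs in full, 2.70.

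**Step 5: single-site change.** Half-width = 1.96 × √(0.5/n). Rural: 25.1 to 17.7 points. An ED with 96 visits: 20.0 to 14.1 points.

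**Step 6: sensitivity.**
- If the stated counts are already alternate-week counts, the unweighted mean change goes from 6.72 to 4.78 points. The narrowing is the same 28.9% and the extra work is still 10%.
- If true changes vary between EDs with SD τ (assumed) and inference extends to other EDs, τ² is added to each ED's variance. With τ = 5 points: 10.70 to 8.35 (22%). With τ = 10: 13.66 to 11.91 (13%). With τ = 20: 21.79 to 20.73 (5%).

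**The case against.** A single systematic rule is a legitimate design. It is simple for the auditors and keeps equally spaced points for the time series. Three further objections have force.

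- **The estimand is loosely worded.** A reader might infer that the plan's main effect would become 29% more precise. The article does not support that. It speaks of an unweighted mean change for each hospital ED and then of a difference between mean changes. It never clearly states an equal-weight average over the four EDs. The analysis named first is the segmented regression. Its weighting is not given, so the gain there is unknown.
- **Workload-neutral versions have a price.** A reader might also infer that the extra charts should be paid for by thinning the centre. At 44% of weeks (998.5 charts, total unchanged) the weighted pooled margin widens from ±2.77% to ±2.86%. At one week in three (750 charts) it widens to ±3.28%. The first cannot be equally spaced. The second leaves about 13 points per 39-week period instead of 19 or 20, at the site with 90% of visits. Neither improves on 6.76 points for the unweighted change (6.77 and 6.80). The objection stands against thinning the centre, but not against adding charts at the other three EDs.
- **Full audit does not make the smallest site readable.** The rural change stays at about ±18 points, limited by visit volume.

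A reader might also take the audit to determine both primary outcomes. For the service outcome it is one source of three, so the audit fraction alone does not set that precision.

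**Conclusion.** The point holds as a cheap improvement in design. It is not an error that undermines the trial's analysis. One common audit fraction gives up precision at the three EDs with the least data, for a saving of about 127 charts per period. The site-level changes, and any equally weighted mean of them, are less precise than they need be.

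The 29% is the narrowing of a confidence interval, not a change in the effect. It assumes p = 0.5, binomial error only and four fixed sites, and applies only to an equally weighted mean. It hardly depends on how the 192 visits split, or on whether the stated counts are already halved. It does depend on between-ED variation once inference goes beyond these four EDs. The rural contrast of ±17.7% with the stated ±12.5% applies only if the stated counts are full visit counts.

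**What to change.** In Health record audits, replace the common rule by a site-specific one:

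- Audit every week, in both 9-month periods, at the rural, community urban and general hospital EDs.
- Keep alternate weeks at the pediatric centre, so that its series stays equally spaced and its own margin is unchanged.
- Weight charts by the inverse sampling fraction wherever visits are pooled across sites.
- State whether 2250, 61 and 2503 are full or alternate-week counts, and quote the margins for the charts that will actually be audited.

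The cost is about 127 more charts per period (about 253 over both periods, roughly 10%), a sampling weight in pooled summaries, and a short edit to the protocol and audit manual. Where the segmented regression needs a common time unit, two-week blocks would fit both sampling rules. The article reports the project as still in its pre-implementation phase and places the chart audits in a later phase, so the rule can be set before abstraction starts.

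### The pooled ±2.0% margin is correct for one proportion in one period over all expected visits, but it describes neither the charts to be audited nor the hospital-level pre/post effect

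*Protocol article*

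**What the plan says.** The precision statement is in Health record audits. From past administrative data, "the number of pediatric MH visits at the pediatric specialized center is expected to be approximately 2250 during each 9-month period", for a margin of ±2.1%, "conservatively assuming a true proportion of 50" per cent. At the other end, "the lowest number of pediatric MH visits during each 9-month period among the other three sites is expected to be approximately 61 at the rural" ED, for ±12.5%. The combined statement is "Pooling across sites, the total sample size in each 9-month period is anticipated to be approximately 2503", for ±2.0%. The article gives no other combined precision and no power figure.

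The same section says that the team will "audit health records of relevant patients seen during alternate weeks in each 9-month pre- and post-implementation period". By Table 4, these audits are the only data source for the primary process outcome, which is "the proportion of patients with documented MH-specific recommendations".

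Under Quantitative analysis, the test of the pathway is a segmented regression of interrupted time series, adjusted for site, with ARIMA autocorrelation. Hospital-level summaries are then added: "An unweighted mean of the change from pre- to post-intervention will be calculated for each hospital ED". The sentence after that defines the main effect measure as a difference of those mean changes.

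**The concern.** Three features of the ±2.0% do not match the rest of the plan.

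- **Sample.** It uses visits over the whole 9 months, while charts are drawn from alternate weeks.
- **Quantity.** It is the margin of a level in one period, while the effect is a change between two periods.
- **Weighting.** It weights by visits, so one ED supplies nearly all the information. The hospital-level summary is unweighted, so a rural ED with about 61 visits could count as much as the pediatric centre with 2250.

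What is at stake is how the results can be read. A combined margin of two points is the only overall statement of precision. A reader who carried it over to the change across the four EDs would expect a resolution that the three small sites cannot give.

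**Working it through.** **Inputs.** From Health record audits: 2250 visits at the pediatric centre, 61 at the rural ED, 2503 in total, p = 0.50, alternate-week auditing (a fraction of about 1/2). From Quantitative analysis: 95% confidence intervals, so z = 1.96, and unweighted hospital changes. The two remaining EDs share 2503 − 2250 − 61 = 192 visits. The rural ED is stated to be the lowest, so each has at least 61, and the split lies between 96/96 and 131/61. The split itself is an assumption.

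**1. Reproduce the stated margins.** Half-width = 1.96 × √(0.25/n).

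| n | Computed | Stated |
|---|---|---|
| 2250 | 2.07% | 2.1% |
| 61 | 12.55% | 12.5% |
| 2503 | 1.96% | 2.0% |

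All three agree. The formula contains no audit fraction, no site weighting and no pre/post contrast.

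**2. Share of one centre.** 2250/2503 = 89.9%. The pooled margin therefore almost repeats the pediatric centre's own.

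**3. Alternate weeks.** If the counts are all visits, n is halved:

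- Pediatric centre: n = 1125, ±2.9%
- Rural ED: n = 30.5, ±17.7%
- Pooled: n = 1251.5, ±2.8%

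**4. Equally weighted mean of four hospital changes.** With independent pre and post samples of equal size and binomial error only, half-width = 1.96 × (1/4) × √(Σ 2 × 0.25/nᵢ).

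- Split 96/96: Σ 1/nᵢ = 0.03767, so 1.96 × √(0.5 × 0.03767)/4 = 6.72 points.
- Split 131/61: Σ 1/nᵢ = 0.04087, so 1.96 × √(0.5 × 0.04087)/4 = 7.00 points.
- With every n halved, each is multiplied by √2: 9.51 and 9.91 points.

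**5. Like-for-like comparison.** The visit-weighted pooled change has half-width 1.96 × √(2 × 0.25/2503) = 2.77 points with all visits, and 3.92 points with alternate weeks. The ratio of unweighted to pooled change is 6.72/2.77 = 2.43 to 7.00/2.77 = 2.53, and it is the same after halving.

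**6. Where the gap from ±2.0% comes from.** Equal weighting contributes a factor of about 2.4 to 2.5, moving from a level to a change contributes √2, and halving contributes a further √2 if it applies.

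**The case against.** The strongest reply is that nothing is miscalculated. The section claims only to estimate a proportion in each period, and it does so correctly. It also discloses the imbalance, because the margins for the largest and smallest sites stand beside the pooled one. All of this stands.

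A reader might infer that pooling visits across unequal EDs makes ±2.0% itself too narrow. The documents do not support that. The EDs are four chosen exemplar sites. With sites fixed, the variance of the pooled proportion is Σ nᵢpᵢ(1 − pᵢ)/N², which never exceeds p(1 − p)/N. Ignoring site therefore does not understate the margin of that quantity.

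A reader might also set ±2.0% against 6.7 to 9.9 points and blame unequal sites for a three- to five-fold shortfall. That mixes the three factors in step 6. Only the factor of 2.4 to 2.5 is due to weighting.

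Nor can a figure near ±10 points be taken as settled. It needs the counts to be total visits, which the article does not say outright. It also needs the main effect measure to be an average over the four EDs. The quoted sentence says the mean is calculated for each ED, and the following one speaks of a difference although there is no second group. The four-ED average is the natural reading but is not written. The hospital summaries are an addition to the segmented regression, whose margin cannot be computed from the article.

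Finally, the outcomes are proportions of patients while the counts are visits, so repeat visitors could reduce the effective number. The article gives no repeat rate, so no size can be attached, and counting one visit per patient would be a design choice, not a correction.

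The mismatch remains. The article chose to state both a combined precision and an effect measure, and the first does not describe the second or the audited sample. This is a discrepancy in the text as printed, not a detail left to a fuller document.

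**Conclusion.** The concern holds as a mismatch, not as an arithmetic error. The ±2.0% is right for one proportion in one period over all 2503 expected visits, 90% of them from one ED.

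- If the counts are all visits, as the wording suggests, the three margins on audited charts are about ±2.9%, ±17.7% and ±2.8%.
- If the main effect measure is the equally weighted mean of the four hospital changes, its margin at 50% is about ±6.7 to 7.0 points with all visits, or ±9.5 to 9.9 points with alternate weeks. Either is 2.4 to 2.5 times the margin of the corresponding pooled change.

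The first result does not depend on how the main-effect sentence is read. The second depends on that reading, on independent pre and post samples of equal size, and on binomial error only. The unknown split of the 192 visits hardly matters. Any variation between sites in the size of the change would widen the second set of figures.

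**What to change.** In Health record audits:

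1. State whether 2250, 61 and 2503 are total visits or visits in the audited weeks.
2. Give the three margins on the audited number. If the counts are totals, these are about ±2.9%, ±17.7% and ±2.8%.
3. Label the pooled figure as a level in a single period, dominated by the pediatric centre.
4. Add the margin of the hospital-level pre/post change: about ±6.7 to 7.0 points if the counts are already audited visits, or ±9.5 to 9.9 points if they are totals. Note that it leaves out between-site variation and is not the margin of the segmented regression.

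In Quantitative analysis, reword the main-effect sentence so that it says whether the four hospital changes are averaged with equal weight. The figure in item 4 applies only if they are.

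The cost is wording and a less favourable stated precision. No patients, charts or visits are added.
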